# REMOTE-ILD study: Description of the protocol for a multicentre, 12-month randomised controlled trial to assess the clinical and cost-effectiveness of remote monitoring of spirometry and pulse oximetry in patients with interstitial lung disease

**DOI:** 10.1136/bmjresp-2023-002067

**Published:** 2024-02-28

**Keywords:** Interstitial Fibrosis, Respiratory Function Test

## Abstract

**Introduction:**

Remote monitoring of home physiological measurements has been proposed as a solution to support patients with chronic diseases as well as facilitating virtual consultations and pandemic preparedness for the future. Daily home spirometry and pulse oximetry have been demonstrated to be safe and acceptable to patients with interstitial lung disease (ILD) but there is currently limited evidence to support its integration into clinical practice.

**Aim:**

Our aim is to understand the clinical utility of frequent remote physiological measurements in ILD and the impact of integrating these into clinical practice from a patient, clinical and health economic perspective.

**Methods and analysis:**

132 patients with fibrotic ILD will be recruited and randomised to receive either usual care with remote digital monitoring of home spirometry and pulse oximetry or usual care alone for 12 months. All participants will complete health-related quality of life and experience questionnaires.

The primary outcome compares the availability of spirometry measurements within the 2 weeks preceding planned clinic appointments. Secondary outcomes will explore other aspects of clinical and cost-effectiveness of the remote monitoring programme.

**Ethics and dissemination:**

The study has been approved by the Camden and Kings Cross Research Ethics Committee (22/LO/0309). All participants will provide informed consent.

This study is registered with www.clinicaltrials.gov (NCT05662124).

The results of the study will be submitted for presentation at regional and national conferences and submitted for peer-reviewed publication. Reports will be prepared for study participants with the support from our public involvement representatives through the charity Action for Pulmonary Fibrosis.

WHAT IS ALREADY KNOWN ON THIS TOPICRegular home spirometry and pulse oximetry are safe and feasible for patients with interstitial lung disease (ILD). However, its utility in supporting clinical decision-making in clinical practice is currently unclear.WHAT THIS STUDY ADDSThis is the first randomised controlled trial of remote monitoring versus usual clinical care in ILD, which aims to establish if there are differences in clinical care and health economic outcomes over a 12-month period.HOW THIS STUDY MIGHT AFFECT RESEARCH, PRACTICE OR POLICYThis study aims to understand whether there is a useful role for remote monitoring in clinical care of patients with ILD and the resource implications required for its incorporation into clinical care.

## Introduction

Interstitial lung disease (ILD) is an umbrella term describing a spectrum of diseases of progressive scarring of the lungs causing progressive breathlessness.^1^ In some cases, for example, in association with autoimmune disease, fibrosis develops following an inflammatory process in the lung parenchyma. In others, fibrosis develops without pre-existing inflammation. The most common form of ILD is idiopathic pulmonary fibrosis (IPF), which has a reported mean incidence of 0.12 cases/10000^2^ and is rising by up to 5% per year.^3^ Treatment of ILD aims to reduce any inflammation to prevent development to fibrosis, reduce development of further fibrosis, reduce lung inflammation and treat symptoms.

Current guidelines for the management of IPF^4 5^ recommend that patients are reviewed by a respiratory specialist every 4–6 months with lung function testing beforehand to monitor progression of disease and response to their current therapeutic regime. There is no formal guidance for the monitoring of patients with other forms of ILD but in the UK most patients are seen approximately 6 monthly with lung function testing.^6^ Lung function monitoring in ILD usually includes assessment of oxygen saturations, spirometry and gas transfer measurements.

Remote monitoring of physiological measurements has been proposed as an additional approach to monitoring chronic diseases. Benefits of remote spirometry and oximetry for patients with ILD have been suggested to include earlier detection of deterioration^7^ or acute illness and personalisation of care,^8^ reduced travel to hospitals,^9^ support of virtual consultations, and increased patient awareness and engagement in management of their lung disease which may support better psychological health.^10–12^

Previous studies have demonstrated that patients with ILD are willing and able to measure their spirometry at home frequently^13–17^ for up to 12 months.^18 19^ These studies have demonstrated that home handheld spirometry correlates well with lab-based spirometry,^7^ although home spirometry often underestimates values compared with lab-based spirometry. Currently, there is no evidence for optimal frequency of spirometry measurements in ILD and no guidelines for spirometry performed outside of a formal lung function laboratory.^20^ A previous randomised controlled trial of remote spirometry uploaded to a bespoke platform via Bluetooth did not meet its primary endpoint of improved health-related quality of life (HRQoL) assessed using the Kings Brief Interstitial Lung Disease Questionnaire but did demonstrate improvements in the psychological domains in those with home monitoring compared with those who did not.^10^

Oxygen saturation is a key physiological measurement of severity of lung disease. Remote pulse oximetry was implemented extensively during the COVID-19 pandemic to manage patients in the community and reduce hospital admissions and appeared to be safe but of limited impact.^21 22^ Preliminary studies by our group have shown that daily home pulse oximetry in patients with ILD for clinician review is feasible over a 3-month period with 83% of participants providing measurements on at least 70% of study days, and 72% of participants providing measurements at least three times/week.^23^

There are limited data regarding the use of remote pulse oximetry for monitoring ILD. It has been demonstrated that short-term continuous oximetry could be used to determine the need for ambulatory oxygen therapy but the economic implications of this were not measured.^24^ Previous studies show that patients with chronic lung diseases, including ILD, found knowing their oxygen saturations reassuring and helped guide their activity levels and oxygen consumption.^25^ Furthermore, clinicians have identified pulse oximetry as the variable that they think would be most beneficial for home monitoring in ILD.^26^

Currently remote monitoring in ILD is not widely used in clinical practice.^27^ Common barriers cited are organisational structure and lack of resources, as well as lack of evidence for efficiency and technical issues.^26^ Other concerns raised about integrating new digital health systems include both data overload, but also that artificial intelligence may not be able to detect subtler nuances, such as missing data may represent periods of either good health or deterioration.^28^

Our randomised controlled study aims to explore whether there is a difference in health and economic outcomes by comparing a cohort of patients who have been asked to monitor their pulse oximetry and spirometry with regular clinical review in addition to their usual clinical care compared with a cohort who are receiving usual clinical care alone.

## Methods and analysis

REMOTE-ILD is a prospective multicentre randomised controlled interventional and observational trial comparing the addition of remote monitoring of home spirometry and oximetry to usual care alone.

### Objectives

The objective of the study is to compare the clinical and cost-effectiveness of remote digital monitoring of home spirometry and pulse oximetry with usual care in the clinical management of patients with ILD.

#### Selection of participants

One hundred and thirty-two participants with fibrotic ILD will be recruited from ILD clinics at participating sites across the UK. Participants must have a diagnosis of fibrotic ILD as confirmed by their local multidisciplinary team meeting with radiological evidence of parenchymal lung fibrosis of any aetiology or radiological or pathological subtype.

A list of recruiting sites is available on www.clinicaltrials.gov and on request from the corresponding author.

Eligible patients who meet the entry criteria will be invited to consent. Most participants will be identified through outpatient clinics but recruitment will not be restricted to this route.

#### Inclusion criteria

Diagnosis of fibrotic ILD as agreed by a specialist ILD multidisciplinary team.Age ≥18 years.Owns a smartphone or electronic tablet device which they are able to use either independently or with support from a carer or family member.Has a mobile telephone number, email address and access to the internet at home.In clinic lung function assessment within the last 6 months prior to study entry including spirometry and gas transfer measurement.Intention for at least two outpatient reviews during the observation period.Willing to allow home monitoring of their health including spirometry and pulse oximetry data.Understands how to use mobile technology (eg, Has downloaded and used other ‘apps’ on their mobile device; uses email).Demonstrates willingness to measure spirometry and pulse oximetry three time weekly for the duration of the observation period.Fluent in English.Written or electronic informed consent.

#### Exclusion criteria

Unable to fulfil all inclusion criteria.Cognitive impairment (which would limit participant’s ability to understand the study or the procedures involved).History of difficulty performing spirometry at previous clinic testing.Contraindications to spirometry (eg, previous pneumothorax, unstable cardiac status, known aortic or cerebral aneurysm).Serious concomitant conditions which place the patient at high risk of respiratory distress.Recent (within the last 6 weeks) or current participation in another interventional clinical research project.

### Study design

The study design is an unblinded randomised control study with parallel arms where participants will be randomly allocated (1:1) to either the remote monitoring arm or usual care arm.

Following informed consent, baseline clinical data collected as part of usual clinical National Health Service (NHS) care will be used for the purpose of the study including previous medical history, all medication usage, previous lung function tests and radiology results. All participants will be asked to complete HRQoL questionnaires (modified Medical Research Council (mMRC) dyspnoea scale, K-BILD Questionnaire, EuroQol 5-Dimension 5-Level (EQ-5D-5L) questionnaire, Generalised Anxiety Disorder-7 (GAD-7) questionnaire) and Patient Activation Measure (PAM) at baseline.

Participants will then be randomly allocated to either the remote monitoring arm or usual care arms.

Remote monitoring arm:

Participants who are allocated to the active remote monitoring arm will be provided with a portable handheld spirometer (Spirobank Smart, MIR, www.spirometry.com) and pulse oximeter (model 3230, Nonin; www.nonin.com) linked to an electronic health application (patientMpower, www.patientMpower.com). Participants will be trained to undertake remote spirometry and pulse oximetry and they will be asked to perform measurements three times per week including two spirometry blows and one resting pulse oximetry reading on each occasion. All readings will automatically be captured via the patientMpower electronic health application and will be immediately visible to their clinical care team via a secure web-based portal. All spirometry attempts will be analysed in real time using artificial intelligence software (ArtiQ, www.artiq.eu)^29^ to assess the quality of the spirometry according to European Respiratory Society (ERS)/American Thoracic Society (ATS) criteria^20^ provided with real time feedback given to participants. Participants will be reminded to record their measurements once weekly.

Participating centres will be asked to monitor these remotely recorded measurements at least every 2 weeks and at, or before, planned clinical assessments. They will be advised that should there be a sustained decrease in either spirometry or pulse oximetry further clinical assessment is recommended.

Participants should continue to have all clinical appointments and medications as per their treating clinician’s recommendations. If there is a clinical decision to discontinue remote monitoring—either for safety/clinical reasons or due to patient choice this should be recorded in the electronic case report form (eCRF).

Usual care arm: These participants will have all clinical appointments and medications as per their treating clinicians’ recommendations.

All participants will be asked to complete health-related QoL questionnaires at 3 months (K-BILD, GAD-7), 6 months (K-BILD, GAD-7, EQ-5D-5L, PAM, modified MRC dyspnoea scale) and at 12 months which is the conclusion of the study.

All clinical observations, appointments, investigations and conversations which occur over the course of the following year will be recorded in the eCRF and analysed.

#### Outcomes

The primary outcome will be measured by comparing the number of clinical appointments where recent spirometry is available for review between the remote monitoring and usual care arms. Recent spirometry is defined as within 2 weeks of the clinical appointment. This will be measured at the first and last clinical appointments in the observation period.

The study hypothesis is that participants who have remote monitoring are more likely to have spirometry available for review at their clinic appointments and that the availability of spirometry is therefore dependent on the method of its collection.

Secondary endpoints of the study are as follows:

Service provision:

Number of clinical reviews per patient.Proportion of clinical reviews which are scheduled, patient initiated and clinician initiated.Proportion of clinical reviews which are virtual versus face to face.Number of in-clinic lung function appointments/patient.Number of patients with chest CT scans.

Clinical:

Proportion of patients with ≥10% decrease in forced vital capacity (FVC) (patient-recorded and hospital) of patient-recorded FVC.Change in FVC over time (patient-recorded and hospital).Number of patients starting antifibrotic medication, new immunosuppression and/or oxygen therapy.Patient-recorded dyspnoea score (mMRC score).HRQoL assessed by the EQ-5D-5L,^30^ K-BILD health status questionnaire^31^ and GAD-7.^32^

Adherence to study measurements:

Adherence to study measurements in active arm.Proportion of patients recording measurements on ≥66% of weeks.Patient engagement and activation assessed by the 13-point PAM questionnaire.^33 34^

Health economic:

Nursing/medical time reviewing data portal.Number of patient contacts with/by remote monitoring clinical team.Number of hospital admissions related to respiratory disease.

The study will be evaluated from a health economics perspective to compare NHS resource use in both arms.

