#### Data analysis plan

The objective of the primary analysis is to determine if the availability of spirometry within 2 weeks of the date of the first and last clinical review within the observation period is independent of the method by which it was obtained (ie, usual care with remote monitoring of spirometry or usual care alone). The primary endpoint variable is the number of outpatient clinical reviews for which spirometry data are available in the 2 weeks prior to the review. The primary endpoint will be assessed at the first and last outpatient clinical review in all patients who have ≥2 clinical reviews during the study observation period. The primary endpoint will be assessed by a χ^2^ test of independence.

All other endpoints will be summarised for descriptive statistical display.

The health economic analysis will be performed adopting the perspective of the NHS and Personal Social Services. NHS healthcare resource utilisation will be assessed using the data from the study and using standard unit cost data (Personal Social Services Research Unit), staff cost time and NHS tariffs. Effectiveness will be measured in terms of differences in quality-adjusted life-years in the two arms, using a linear approximation method, assuming the change in the utility over time is linear. Costs and effectiveness in both arms will be compared and the results presented in terms of incremental cost-effectiveness ratio.

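### The primary endpoint has conflicting scoring rules, and two of the three sections that define it let a review triggered by remote monitoring count as the first or last scored visit

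*Protocol article*

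**What the plan says.** The protocol article describes the primary endpoint in three places.

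- **Abstract, Methods and analysis.** The comparison is of "availability of spirometry measurements within the 2 weeks preceding planned clinic appointments". The window looks back only, and the visits are planned ones.
- **Outcomes.** "Recent spirometry is defined as within 2 weeks of the clinical appointment", and "This will be measured at the first and last clinical appointments in the observation period". The window has no direction, and the visits are not limited to planned ones.
- **Data analysis plan.** The objective refers to "availability of spirometry within 2 weeks of the date of the first and last clinical review within the observation period", again without direction. The endpoint variable in the same paragraph is "the number of outpatient clinical reviews for which spirometry data are available in the 2 weeks prior to the review", which looks back only. Neither sentence limits the visits to planned ones. Scoring takes place "in all patients who have ≥2 clinical reviews during the study observation period".

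Two other statements bear on this. Study design advises centres, for the remote arm, that "should there be a sustained decrease in either spirometry or pulse oximetry further clinical assessment is recommended". The secondary endpoints in Outcomes divide clinical reviews into scheduled, patient-initiated and clinician-initiated, so an unscheduled contact is a clinical review in the article's own terms.

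**The concern.** This is the only endpoint with a planned hypothesis test; the Data analysis plan says that all others are summarised descriptively. The trial is unblinded. If the scoring rule can be read in several ways, it can be settled after the data are seen, and the same visit can pass or fail depending on the section followed.

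The type of review matters more than the wording of the window. Home readings exist only in the remote arm, so only that arm can have a review prompted by a fall in them. Such a review very probably has spirometry within the preceding two weeks. If it may be scored as the first or last review, the intervention affects which visits enter the comparison as well as whether spirometry is available at them. Randomisation does not protect against that. The requirement for two or more reviews adds to it: a remote-arm patient with one scheduled and one triggered review is analysed, while a comparable usual-care patient with one scheduled review is not.

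**Working it through.** **The plan's own figure.** The article gives 108 evaluable and 132 recruited participants for Cohen's w = 0.30, 80% power and 82% completion. Using the noncentral chi-square with noncentrality N·w² and an assumed alpha of 0.05, N = 108 reproduces with 2 degrees of freedom (power 0.804); 1 degree of freedom would give 88. Recruitment reproduces as 108/0.82 = 131.7, rounded up to 132. The degrees of freedom are a separate matter, and nothing below depends on them. The figure is used only to set 108/2 = 54 evaluable patients per arm.

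**Two test cases against the four statements.**

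| Statement | Only spirometry is 10 days after the visit | Triggered outpatient review falls first or last |
|---|---|---|
| Abstract | not counted | not scored |
| Outcomes | counted, read literally | scored |
| Data analysis plan, objective | counted, read literally | scored |
| Data analysis plan, endpoint variable | not counted | scored |

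The statements disagree on both cases, and the Data analysis plan disagrees with itself on the first.

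**Size of the review-type effect.** Inputs:

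- q: availability at planned reviews in the remote arm. Values tried are 79% (the 2019 clinic figure in Sample size calculation, which states neither window nor review type), 92% (assumed) and 96% (the median weekly adherence in the earlier home-spirometry study cited there, used as a proxy).
- f: share of scored remote-arm reviews that were triggered by monitoring. The documents do not give it; 10%, 20% and 30% are assumed.
- Availability at a triggered review: set to 100%, which gives an upper bound.

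Measured remote-arm availability = (1 − f)·q + f·1. Subtracting q, the inflation is f·(1 − q).

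| q | f = 10% | f = 20% | f = 30% |
|---|---|---|---|
| 79% | 0.10 × 0.21 = 2.1 points | 4.2 | 6.3 |
| 92% | 0.10 × 0.08 = 0.8 points | 1.6 | 2.4 |
| 96% | 0.10 × 0.04 = 0.4 points | 0.8 | 1.2 |

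**Effect on the test when there is no true difference at planned reviews (79% in both arms).** The chance of a significant result favouring remote monitoring is Φ[(d − 1.96·SE₀)/SE₁], where d is the spurious difference, SE₀ the pooled and SE₁ the unpooled standard error. The nominal value in that direction is 2.5%.

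- 54 per arm: 4.6%, 8.0% and 13.4% for f = 10%, 20% and 30%.
- 108 scored reviews per arm (two per patient, treated as independent): 5.8%, 12.0% and 22.6%.

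**Effect of the window wording.** Remote-arm patients are asked to measure three times a week, so counting tests done after the visit would add few passes there and would mainly add them in usual care. If that raised usual care from 79% to 84% (assumed), power against 96% with 54 per arm would fall from 77% to 55%. This works against the remote arm, the opposite direction to the review-type effect.

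**The case against.** The best reply on the window is that its intended direction can be recovered. The sentence that names the endpoint variable looks back, the abstract looks back, and Outcomes speaks of spirometry being there to review at the appointment. That stands: the undirected wording is loose drafting to be tidied. It does not rescue the review type, because if the body of the article governs over the abstract, no restriction to planned visits remains.

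It can also be said that the bias is modest and cannot be sized from the documents. A triggered review must fall first or last to be scored, the trigger may be oximetry alone, and nothing says how soon the assessment follows. This stands too, and is why recent spirometry at such a review is called very probable rather than certain.

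A reader might infer more than the documents support, in three ways.

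- **That the varying windows themselves favour the remote arm.** They do not; the effect runs mainly the other way, as shown above.
- **That the inflation is much larger.** Suppose 20% of scored reviews are unplanned in both arms, with availability at those reviews of 100% in the remote arm and 50% in usual care, and planned-review rates of 92% and 79%. The measured rates are 0.8 × 92 + 0.2 × 100 = 93.6% and 0.8 × 79 + 0.2 × 50 = 73.2%, a difference of 20.4 points against 13. Of the extra 7.4 points, only 1.6 arise in the remote arm. The other 5.8 rest on the assumed 50%, which no passage supports, and missing spirometry at an unplanned usual-care visit would be a real difference in availability.
- **That blow quality, or a window reaching back before randomisation, is part of the fault.** The endpoint is availability, and the article describes software grading for feedback to participants without saying that grades enter the trial data. Spirometry from before randomisation would be balanced between arms and would dilute the contrast. Both are analysis-plan detail.

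**Conclusion.** The point holds as an inconsistency in the definition of the only tested endpoint, with a possible bias towards the remote arm that comes from review type alone. Its upper bound is f(1 − q): 2.1 to 6.3 points if remote monitoring adds nothing at planned visits (q = 79%), 0.8 to 2.4 points at q = 92%, and about 1 point or less at q = 96%, for f between 10% and 30%. All of this rests on an assumed f and on full availability at triggered reviews. The effect is therefore small if home adherence is as high as the sample size section expects, and matters most if the true benefit at planned visits is small. The window ambiguity is a second, separate defect, and would mainly raise usual care. The documents do not show that the result will be materially biased. They do show that the endpoint cannot be scored unambiguously as written.

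**What to change.** Use one definition in the abstract, Outcomes and Data analysis plan: spirometry dated in the 14 days up to and including the date of the first and last scheduled outpatient review in the observation period. Select those reviews with the scheduled, patient-initiated or clinician-initiated classification that the secondary endpoints already require. Change the analysis set to match, namely patients with at least two scheduled reviews; otherwise a patient with one scheduled and one triggered review would qualify with a single scorable visit. Report unscheduled reviews separately, or give the all-reviews version as a sensitivity analysis. Settle this before outcomes are compared by arm.

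The cost is a wording amendment. No new data item is needed, since all appointments and investigations go into the eCRF, and the stated 108 and 132 do not change. The downside is that slightly fewer reviews are scored. No blow-quality rule and no minimum interval after randomisation is needed for this purpose.
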